## Abstract

**Background:**

The presence of chemicals in the environment is ubiquitous. Human biomonitoring studies have shown that various chemicals can be detected in the majority of the population, including pregnant women. These compounds may pass the placenta, and reach the fetus. This early life exposure in particular may be detrimental as some chemicals may disrupt the endocrine system, which is involved in various processes during development. The LINC study is a prospective birth cohort designed to study associations between early life environmental exposures and child health, including growth and neurodevelopment. The purpose of this paper is to give an overview of this cohort.

**Methods and design:**

Recruitment for this cohort has started in 2011 in three Dutch areas and is still ongoing. To date over 300 mother-child pairs have been included. Women are preferably included during the first trimester of pregnancy. Major congenital anomalies and twin births are reasons for exclusion. To assess exposure to environmental chemicals, cord blood, placenta, meconium and vernix are collected. Parents collect urine of the child shortly after birth and breast milk in the second month of life. Exposure to a broad range of environmental chemicals are determined in cord plasma and breast milk. Furthermore various hormones, including leptin and cortisone, are determined in cord plasma, and in heel prick blood spots (thyroxine). Data on anthropometry of the child is collected through midwives and youth health care centres on various time points until the child is 18 months of age. Furthermore cognitive development is monitored by means of the van Wiechen scheme, and information on behavioral development is collected by means of the infant behavior questionnaire and the child behavior checklist. When the child is 12 months of age, a house visit is scheduled to assess various housing characteristics, as well as hand-to-mouth behavior of the child. At this visit exposure of the child to flame retardants (with endocrine disrupting properties) in house dust is determined by means of body wipes. They are furthermore also measured in a saliva sample of the child. Next to these measurements, women receive questionnaires each trimester regarding amongst others lifestyle of the parents, general health of the parents and the child, and mental state of the mother.

**Discussion:**

This study was approved by the medical ethics committee of the VU University Medical Centre. Consent for the infant is given by the mother, who is specifically required to give consent for both herself as well as her child. Results will be published regardless of the findings of this study, and will be widely disseminated among related medical stakeholders (e.g. midwives and pediatricians), policy makers, and the general public.

## Background

Chemicals are used worldwide, making everyday life more comfortable. Their integration into modern day society extends to a level that consumers are often unaware of their presence. They are incorporated in common items, e.g. food packaging materials containing bisphenol a (BPA) and phthalates, which may transfer from the packaging material to the food item itself [1]. Furthermore food products and water may contain pesticides, including those banned from production but persistent in the environment [2]. This ubiquitous presence of chemicals inevitably results in human exposure.

Human biomonitoring studies in the United States detected several chemicals such as perfluorinated alkyl acids (PFAAs) and polychlorinated biphenyls (PCBs) in 90–100 % of the population [3], including pregnant women [4]. They have also been quantified in amniotic fluid [5, 6] and cord blood [7, 8], which indicates that they may pass the placenta and reach the foetus. As the presence of contaminants has also been established in breast milk [9], it is clear that exposure not only starts prenatally, it also continues in early life.

Research has shown that certain compounds may interfere with the function of hormones (endocrine disrupting chemicals, EDCs), including thyroid hormones, estrogen, and testosterone (reviewed by Bergman et al. [10]), which are involved in various processes in adults, but also in brain development early in life [11, 12]. They may also interact with peroxisome proliferator activated receptor α and γ, involved in amongst others adipogenesis [10]. Furthermore, exposure early in life may cause epigenetic modifications, resulting in increased expression or silencing of genes - effects which may be trans-generational [13]. Another point to consider is that exposure early in life may have different effects than exposure in adulthood, as developmental plasticity is much higher in the first period of life [14].

An increasing number of children nowadays face the diagnosis of diabetes type 2 [15], obesity [16, 17], attention deficit hyperactivity disorder [18], autism spectrum disorder [19], and other behavioral disorders. Even though increased risks for each of these health problems have been observed with increased exposure to chemicals [20–22], results are not unambiguous and variations in methodology complicate comparison between different studies. Furthermore, the focus in most observational research has been on non-dioxin-like PCBs and dichlorodiphenyldichloroethylene (DDE), while other compounds such as perfluorinated alkyl acids, and phthalates have been identified as potential health threats as well, but have not yet been investigated as thoroughly.

For most non-communicable diseases important risk factors has been well established, e.g. the role of diet and physical activity in the etiology of obesity and diabetes type 2. However, the increasing prevalence of these diseases in children and their impact on society and health care costs, has created a need to further explore the role of environmental factors. This has led to calls from the European Union to motivate research on this particular topic. As a result, the LInking EDCs in maternal Nutrition to Child health (LINC) study has been set up to investigate health effects of perinatal exposure to a variety of EDCs, and to study determinants of exposure, including parental lifestyle, maternal dietary intake, the residential and occupational environment, and child behaviors. The purpose of this paper is to give an overview of this cohort, for which recruitment has started in 2011, and is currently still ongoing. Study protocols as they currently are used will be reported, including future plans for follow-up. We will furthermore describe the strengths and limitations of this cohort, as well as its’ potential in light of current scientific challenges.

## Methods

The LINC study is a population-based, prospective birth cohort study. It has been initiated to study the effects of perinatal exposure to EDCs on various health outcomes later in life. The general aims of the study are (Fig. 1):

**Fig. 1 Fig1:**
[figure not shown]
Overview of study aims

To relate early life exposure markers of EDCs with effect biomarkers, child health outcome data and other parameters via multiple regression and multivariate analysis, while taking into account relevant confounders and covariates.To determine factors which are relevant for exposure to EDCs, including, parental lifestyle factors, maternal diet, factors in the residential and/or occupational area, and child behavior types.

### Subjects

All children without major congenital anomalies who are born to women living in the area of Zwolle, Purmerend, or Den Helder (Fig. 2 [23]) are allowed to participate in the cohort. The area of Zwolle in particular was chosen because of the relatively low level of urbanization; about 59 % of the Zwolle city area is used for agriculture. Purmerend and Den Helder differ substantially from Zwolle, both from an environmental and demographic perspective. Purmerend for example is a primarily urban region, and has a higher percentage of population of non-western origins compared to Zwolle (15.1 % vs. 10.0 %). Den Helder on the other hand is characterized by fishery, and a large naval base. Moreover, there is a relatively high number of teen pregnancies (between 0.81–1.53 against 0.6 in the general Dutch population). However, these regional differences offer the opportunity to compare results for different populations.

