**Fig. 2 Fig2:**
[figure not shown]
Population density in the Netherlands 2012

In the Netherlands, primary care during pregnancy is given by midwives, with obstetricians only involved in complicated pregnancies. Furthermore it is not uncommon for deliveries to occur in the home environment: between 2011 and 2013 approximately 20 % of births were at home [24]. Pregnant women have therefore been recruited through midwifery clinics from 2011 and onwards. Recruitment started in 2011 in Zwolle, after which Purmerend and Den Helder were added as locations. Recruitment in these latter locations is still ongoing, but was finished in Zwolle in 2013. To date over 300 mother-child pairs have been included. Women less than 12 weeks pregnant at their first visit to the clinic are preferred for inclusion, however women may also be included at later stages in pregnancy. They are considered eligible for participation if they are able to fill out questionnaires in Dutch. Decisionally incapacitated subjects are not asked to participate, and twin pregnancies are excluded.

Thus far eight midwifery clinics have been involved in recruitment. Of these, six are located in the area of Zwolle. Midwifery clinics are chosen based on the number of hospitals they cooperate with in the area. If transfer options are limited to one hospital, the clinic is eligible for participation, as this facilitates tracking of child births which do not occur in the home situation. In Zwolle, where recruitment is already finished, about one in fifteen women agreed to participation.

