### Statistical analyses

For all analyses effect modification of the outcome by gender will be checked, as the included chemicals disrupt the endocrine system, and in particular steroid hormones. Linearity of exposure markers and outcome will furthermore be checked due to suspected nonmonotonic dose-response associations [62]. Next to that, various methods will be considered for dealing with exposure values below the limit of quantification (LOQ), including replacement by LOQ/√2 [63], and multiple imputation [64].

In order to quantify the relation between exposure and BMI at the age of 12 and 18 months, we will use linear multilevel (mixed) models. These models take into account the dependency of repeated measures within the individuals. For each compound a separate model will be composed for weight, height, BMI, and head circumference. Exposure quartiles, time, and gender will be added to the models as fixed effects and a random effect will be added for subject. Various covariates, described in 2.5.1, will be tested and included in the model if significant (change in β-coefficient > 10 %).

To study the relationship between exposure and behavior at the age of 18 months, linear regression analyses will be conducted. Both syndrome and DSM-oriented scales from the CBCL will be used for analysis. Syndrome scales are: Emotionally Reactive, Anxious/Depressed, Somatic Complaints, Withdrawn, Attention Problems, Aggressive Behavior, and Sleep Problems. DSM-oriented scales are: Affective Problems, Anxiety Problems, Pervasive Developmental Problems, Attention Deficit/Hyperactivity Problems, and Oppositional Defiant Problems. The overall scales ‘Externalizing’ and ‘Internalizing’, and the total score were also used.

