#### Covariates

Potential covariates were selected based on literature. Weight and length of both parents are measured by the midwife at inclusion, approximately 10–12 weeks in pregnancy. Measurement of maternal weight is repeated at 36 weeks of pregnancy to determine gestational weight gain. Gestational age is determined by means of ultrasound. Birth weight is measured by a midwife or a nurse and is obtained from registries of the midwives.

Questionnaires are administered at inclusion and the start of the second trimester to collect information on education (having a bachelor or master degree, yes or no), birth date of the mother, parity, and maternal smoking (yes or no) and alcohol intake during the first trimester (drinks per week). At inclusion, fish intake (grams per day) is determined by food frequency questionnaire which includes both frequencies and portion sizes [49]. One month after birth another questionnaire is administered to inquire on the use of medication during pregnancy, including folic acid intake (yes or no).

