The population of the LINC study is very homogeneous, which is an advantage as associations are less likely to be confounded by demographic or socio-economic factors. Extrapolation of results to the general population or other specific groups should be done with caution. Another point is that a relatively small number of respondents is included in the cohort. About one in fifteen pregnant women agreed to participation. A large proportion of the women declined to participate due to the study duration and the anticipated burden of the tasks associated with the study during pregnancy and after birth - periods which were already perceived as quite intense by most potential participants. However, as this is a prospective birth cohort, no selections in study population are made. All women are eligible for participation, unless they are unable to fill out the Dutch questionnaires. These cases have thus far been extremely rare.

Efforts are made to keep drop-out rates as low as possible, amongst others by regularly sharing results of the study and translating these to daily life applications. However, due the duration of the study for each participant, loss to follow-up is inevitable. Thus far 67 participants dropped-out, which is approximately 22 %. This is lower than expected from other studies, and this percentage of drop-out was taken into account in the power calculations. For publications participants included in the study will be compared to participants who were excluded or dropped-out. Next to that, the LINC study has been designed in cooperation with other prospective mother-child cohorts within Europe, which also focus on early life environmental chemical exposure. The main reason for doing as such, is to facilitate cooperation for data-analysis. Through these common efforts, sufficient statistical power can be achieved to study the health effects of environmental chemicals.

In conclusion, the LINC study, as a prospective cohort, will provide insight into the effects of early life exposure to EDCs on child health and development, including childhood obesity and neurodevelopmental disorders. Knowledge on the etiology of these childhood disorders is valuable as this may enable more effective prevention and intervention. Our aim is to extend follow-up of our participants throughout childhood and hopefully adolescence and adulthood to further study long-term health effects of environmental exposures.

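### Recruitment area is neither a model term nor a candidate covariate, although the article says the three areas differ substantially in environment and demography

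*Protocol article*

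**What the plan says.** **The areas.** The Subjects section states: "Purmerend and Den Helder differ substantially from Zwolle, both from an environmental and demographic perspective". It adds that "about 59 % of the Zwolle city area is used for agriculture", that Purmerend is mainly urban with a larger share of residents of non-western origin (15.1% against 10.0% in Zwolle), and that Den Helder has fishery, a naval base and more teen pregnancies. It concludes: "However, these regional differences offer the opportunity to compare results for different populations".

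**Recruitment period.** Recruitment began in Zwolle in 2011 and the other two areas were added afterwards: "Recruitment in these latter locations is still ongoing, but was finished in Zwolle in 2013". Six of the eight clinics are in the Zwolle area.

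**The model.** For the growth outcomes, Statistical analyses says: "Exposure quartiles, time, and gender will be added to the models as fixed effects and a random effect will be added for subject". Further covariates come from a numbered subsection, which can only be Covariates, and are kept if they move the coefficient by more than 10%. For behaviour at 18 months the section specifies linear regression and names no separate adjustment set. Effect modification is planned for gender only.

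**The covariates.** The subsection opens: "Potential covariates were selected based on literature". It then covers parental weight and length, gestational weight gain, gestational age, birth weight, education, maternal birth date, parity, smoking, alcohol, fish intake and medication including folic acid.

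**The later statement.** Strengths and limitations says: "The population of the LINC study is very homogeneous, which is an advantage as associations are less likely to be confounded by demographic". The sentence goes on to include socio-economic characteristics as well.

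**The concern.** A confounder must be related to both exposure and outcome. On the article's own account, area plausibly is. On the exposure side, the aims list residential factors as a determinant of exposure, and the areas are described as agricultural, urban and fishing, while pesticides and methylmercury are among the chemicals to be measured. On the outcome side, the areas are said to differ demographically, and the Discussion itself treats demographic and socio-economic factors as potential confounders.

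Area is also partly tied to birth year, because Zwolle closed in 2013 while the other two areas continued. The word time in the growth model, read in context, is follow-up time within the child and would not pick this up.

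Followed as written, the analysis lets any residual difference in growth or behaviour between the areas be attributed to whichever chemicals also vary between them. The 10% rule gives no protection, because area is never put forward to be tested.

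**Working it through.** **1. Is area in the analysis under another name?**

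| Regional contrast in Subjects | Individual-level counterpart in Covariates |
|---|---|
| Teen pregnancy (Den Helder) | Maternal birth date |
| Fishery (Den Helder) | Fish intake, a possible partial proxy |
| Other demographic differences | Education, parity, smoking, alcohol: partial |
| Non-western origin, 15.1% v 10.0% | None |
| Agricultural v urban setting | None |
| Recruitment period (Zwolle closed 2013) | None |

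The last three rows remain uncovered.

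**2. How large could the bias be?** The article gives no BMI by area, no exposure by area and no regional split of participants, so there is no figure of its own to reproduce. For scale, take one area against the other two combined:

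bias ≈ γ × (p_H − p_L)

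Here γ is the difference in mean BMI between that area and the rest that remains after the listed covariates, and p_H and p_L are the shares of children from that area in the high and low exposure groups. Both inputs are assumptions. Bias in kg/m²:

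| γ (kg/m²) | 10 points | 20 points | 30 points | 40 points |
|---|---|---|---|---|
| 0.2 | 0.02 | 0.04 | 0.06 | 0.08 |
| 0.3 | 0.03 | 0.06 | 0.09 | 0.12 |
| 0.5 | 0.05 | 0.10 | 0.15 | 0.20 |

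The Sample size section treats 1.0 kg/m² between high and low exposure as relevant. Against that the range is 0.02/1.0 = 2% to 0.20/1.0 = 20%. Three of the twelve cells exceed 10% of that target and one equals it. In most of the grid, area would not have met the article's 10% rule for an effect of that size.

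**3. What does including area cost?**

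- *Degrees of freedom.* Use the F test for one added exposure term, with λ = N × ΔR² / (1 − R²_full), N = 200 and ΔR² = 0.05. The article does not state the full-model R², so two values are shown. With 10 or with 12 variables, power is 0.898 (R²_full = 0.05) or 0.989 (R²_full = 0.45). The two extra parameters make no visible difference.
- *Correlation with exposure.* For two equal exposure groups with 70% and 30% from one area (a 40-point difference), the correlation is 0.4. The variance inflation is 1/(1 − 0.4²) = 1/0.84 = 1.19, so the standard error rises by √1.19 = 1.09, about 9%. Dividing λ by 1.19 takes it from 10.53 to 8.84 and from 18.18 to 15.27, and power becomes 0.841 and 0.973. At a 10-point difference the inflation is 1/(1 − 0.01) = 1.01.

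**The case against.** **The two descriptions need not conflict.** A reader might infer that the article contradicts itself and dismisses confounding. The text does not support that. The Subjects section describes the source areas; Strengths and limitations describes the women who enrolled. Enrolment is self-selected (about one in fifteen agreed), requires Dutch questionnaires and draws on six Zwolle clinics out of eight, so varied towns could yield a uniform cohort. The Discussion says confounding is less likely, not absent, and covariate adjustment is still planned. What stands is that the article does not draw this distinction and gives no cohort data for homogeneity.

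**Measurement differences between areas.** It is tempting to add that different clinics and youth health care staff take the measurements. The article describes standardised follow-up protocols, trained staff, similar instructions to midwives and youth health care, daily calibration of midwives' scales and one laboratory per compound. The point does not rest on this strand.

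**A promised regional analysis.** The article mentions an opportunity to compare regions and commits to nothing. With about 200 sampled children and two clinics outside Zwolle, an interaction would probably be imprecise.

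**Over-adjustment.** If area affects the outcome only through exposure, conditioning on it discards real exposure contrast. This is a fair objection and the reason to show results both ways. Year of birth also overlaps with area, though only partly: start dates for the later areas are not given, and recruitment may have overlapped.

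**A candidate covariate would be enough.** This is defensible. Applied compound by compound, however, the 10% rule could place area in some models and not in others, which makes results across chemicals harder to compare.

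**An article condenses the plan.** This does not answer the point, because the fixed effects, random effect, covariates and selection rule are all written out.

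**Conclusion.** The point holds as an analysis choice worth correcting. The article describes areas that differ in environment and demography, treats residential area as a possible source of exposure, and then sets out a model and a covariate list that give area no way in. Existing covariates deal with part of the difference; setting, ethnicity and recruitment period remain.

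The size is unknown. The 0.02 to 0.20 kg/m² range rests entirely on assumed regional BMI differences of 0.2 to 0.5 kg/m² and assumed mix differences of 10 to 40 points, and setting it against 1.0 kg/m² only gives scale. A reader might infer that a substantial part of any chemical effect would be a regional artefact. The documents support only that this is left unexamined, and that at the lower end it would be negligible. The homogeneity statement sits uneasily with the Subjects section but is not shown to be false.

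**What to change.** - Add recruitment area (three levels) as a fixed effect in every exposure-outcome model, for growth and for behaviour, outside the 10% rule. Report estimates with and without it.
- Add year of birth at least as a sensitivity analysis, since it partly overlaps with area.
- Label any exposure-by-area comparison as exploratory.
- Under Strengths and limitations, either support the homogeneity statement with cohort characteristics by area or limit it to the enrolled women and acknowledge the differences between the source areas.

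**Cost.** No new data collection: area follows from the recruiting clinic and year of birth from the birth record. Area takes about two degrees of freedom; year of birth takes one or more further. Precision falls modestly where area and exposure are correlated, with a variance inflation of about 1.2 at a 40-point mix difference and close to 1.0 at 10 points.
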